### Child Sleep Habits Questionnaire (CSHQ)

The Children’s Sleep Habits Questionnaire (CSHQ) will be completed at baseline by all children participating in Stage One and at post-intervention by all children participating in Stage Two.

This questionnaire, for children aged 4 to 12 years, is designed to screen for the most common sleep problems in that age group. The CSHQ focuses on sleep disorders common to this age group in three domains: Dyssomnias (difficulty getting to sleep or staying asleep, Parasomnias (sleepwalking/talking, night terrors, bedwetting, restless leg syndrome, etc), and Sleep-Disordered Breathing (Owens 2000).

In a 10% subset of children in Stage Two of the study, the duration of night-time sleep and sleep latency will be recorded by additional subjective (sleep diary) and objective means (actigraphy).

### Sleep Diary (see Appendix A)

Parents of the children whose sleep will be objectively measured will be asked to document on the form their child’s bed time and the time that they arise, indicating any intervals where the actigraph may be removed, and periods of sleep. The diary therefore allows parental perception of their child’s sleep to be documented and can be crosschecked with the actigraph data.

### Actigraphy

Actigraphy is the use of accelerometers to measure human movement. This technique has been used world-wide in a variety of research and clinical situations, and provides simple, objective measures of sleep efficacy without the need for intrusive electrode monitoring. The actigraph is worn on the wrist and the movement of the wrist is monitored continuously whilst it is being worn. The actigraph is very light-weight and can be used on individuals of all ages for long periods of time. Wrist movement data is processed within the unit and by subsequent software programs to give an indication of general activity levels.

At the pre-treatment baseline, parents will be asked to ensure that their child wears the actigraph at night for 5 nights. Post-intervention, they will be asked to do the same for a further 5 nights. Using the actigraph Sleep Analysis software, the following information will be recorded for each night of the sleep study period:

- total sleep time
- total wake time
- sleep onset latency
- number of awakenings

Data for each of these variables will be averaged over the 5-night period.

# STATISTICAL CONSIDERATIONS

## Method of Randomisation

Randomisation of children in stage two will be performed centrally at the Centre for Statistics in Medicine in Oxford (CSM) using dedicated computer software. Following recruitment and consent, participants’ details will be faxed to the CSM. The randomisation programme will include a minimisation algorithm to ensure balanced allocation of participants across the treatment groups for school (to allow for any sociodemographic/school differences) and sex of the child (an important prognostic factor). The first 36 patients (10%) will be allocated randomly without the minimisation factors to avoid predictability. The minimisation algorithm will be applied with an allocation ratio that is not fully deterministic. Fifteen percent of the sample will be randomly selected to use the objective sleep monitors (allowing for some refusals). The statistician carrying out the randomisation will have no direct contact with participants so allocation will be totally independent of patient recruitment.

## Outcome Measures

Stage Two (RCT)

### Primary outcome

- Can supplementation with Omega 3 (DHA) improve child behaviour and learning in underachieving children aged 7-9 years? Outcomes assessed will include reading performance, working memory and ADHD-type symptoms (inattention, hyperactivity, impulsivity) as rated by teachers and parents.

### Secondary outcome

- Might any treatment effects on behaviour or cognition be mediated by changes in child sleep? (measured subjectively in all participants and objectively in a subset)

### Stage One (Observational study)

Secondary outcomes

- Do children’s levels of DHA or related fatty acids (assess objectively via a pinprick blood sample) predict their learning, behaviour or sleep?
- Are any changes in behaviour or cognitive performance associated with changes in blood fatty acid status?
- Do sleep measures (and any changes in these) relate to objective measures of blood fatty acid status?

## Sample Size

At Stage One, our previous studies indicate that a sample of 600 participants will be needed to identify an adequate number of eligible participants* for the intervention study, for which power calculations have been carried out (see below). This number of Stage One participants will also provide sufficient variance on all secondary outcome measures to ensure valid correlational analyses between these.

*Recruits to Stage Two must show ‘room for improvement’ on the main primary outcome (i.e. scoring within the lowest tertile on age-standardised measures of reading).

Following the only previous randomized controlled study to assess reading ability, power calculations were performed to estimate likely group sizes ([name] & [name], 2005)). These indicated that with significance set at 5% and power at 90%, groups of 180 (i.e. a total n of 360) would be required, based on our standardized reading change. Other outcomes would have required smaller sample sizes.

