# PROTOCOL SUMMARY

**Title:** The DHA (docosahexaenoic acid) Oxford Learning and Behaviour (DOLAB) Study.

**Type of Study:** The study has two stages: Stage One is an

observational study and will be followed by Stage Two, a randomised controlled trial.

**Population:** Up to 600 children aged 7 years to 9 years from mainstream schools who are currently underperforming in reading (lowest tertile on nationally standardized achievement tests) will be included in Stage One of the study. 360 of these children will go on to be included in Stage Two, the randomised controlled trial.

**Number of Sites:** Up to fifty schools in Oxfordshire (and Buckinghamshire and Berkshire if required).

**Intervention:** The active compound (DHA, 600mg per day) and placebo (matching in package, taste and appearance) will be administered in an oral supplement.

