## Loss to Follow-up

If any of the trial patients are lost to follow up, contact will initially be attempted through the school and parent address, otherwise missing data will be imputed using median values by treatment group.

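### The 90% power for 180 per group holds only if reading outcomes are essentially complete, because exactly 360 children are randomised with no stated allowance for loss

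*Protocol*

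**What the plan says.** The Sample Size section reports a calculation "with significance set at 5% and power at 90" per cent and concludes that "groups of 180 (i.e. a total n of 360) would be required, based on our standardized reading change". Its only account of the effect is that last phrase, which refers to one earlier randomised study. No mean difference, SD or sidedness is given, and attrition is not mentioned.

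The number entering the trial is the same. The Protocol Summary says "360 of these children will go on to be included in Stage Two, the randomised controlled trial", and the Design section repeats 360. The Method of Randomisation section agrees: "The first 36 patients (10%) will be allocated randomly without the minimisation factors to avoid predictability", and 36 / 0.10 = 360.

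The sections on participant transfer and withdrawal and on loss to follow-up cover voluntary withdrawal, change of school, complete withdrawal without a reason, and loss of contact. The last begins "If any of the trial patients are lost to follow up" and ends "otherwise missing data will be imputed using median values by treatment group". The Analysis Plan repeats the group-median rule for missing data in general. No loss rate is given anywhere.

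**The concern.** A number described as required for 90% power is normally the number of children who supply the outcome. Here it is also the number randomised, so no child can be lost without going below the stated requirement. A child withdrawn completely will usually have no 16-week reading score, and so no change score, which is the quantity on which the trial was sized.

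The protocol does allow a margin elsewhere: the Method of Randomisation section selects 15% of children for the sleep monitors to cover refusals, against a 10% subset in other sections. It states no such margin for the reading outcome.

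What is at stake is the meaning of the 90%. The Primary Endpoint section aims to confirm or refute a benefit, and readers will judge the result against that figure. The group-median rule hides the issue, because the analysed count stays at 360 however many outcomes were observed.

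**Working it through.** **Inputs from the protocol.** Significance 5%, power 90%, 180 per group, 360 randomised, analysis of change scores, missing values replaced by the group median.

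**Assumptions, because the protocol is silent.** Two-sided test; loss rates of 5%, 10%, 15% and 20%, equal in both groups.

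**Step 1: what 180 per group implies.** The figure cannot be reproduced forwards without an effect size and SD. Solving backwards with the normal approximation for two means:

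d = (z for 97.5% + z for 90%) × √(2/n) = (1.960 + 1.282) × √(2/180) = 0.342 SD.

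The noncentral t gives 0.343. A one-sided 5% test would give 0.308. This shows only what 180 implies; it cannot show whether 180 already contains a margin.

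**Step 2: power when fewer outcomes are observed.** Power = Φ(d × √(n/2) − 1.960), with n = 180 × (1 − loss). To keep 180 observed per group, randomise 180 / (1 − loss) per group.

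| Assumed loss | Observed per group | d × √(n/2) | Power | Total to randomise for 180 observed per group |
|---|---|---|---|---|
| 0% | 180 | 3.242 | 90.0% | 360 |
| 5% | 171 | 3.159 | 88.5% | 380 |
| 10% | 162 | 3.075 | 86.8% | 400 |
| 15% | 153 | 2.989 | 84.8% | 424 |
| 20% | 144 | 2.899 | 82.6% | 450 |

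The noncentral t gives 88.5%, 86.7%, 84.8% and 82.6%. One-sided testing gives 88.6%, 87.1%, 85.4% and 83.5%. Power falls to 88% at a loss of about 6.5%.

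**Step 3: does group-median imputation restore the power?** Simulation used normal data, losses completely at random, a t-test on all 180 per group after median filling, and 20,000 runs per setting.

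| Assumed loss | Rejections at d = 0.342 | Rejections with no effect |
|---|---|---|
| 0% | 89.6% | 4.8% |
| 10% | 90.6% | 7.8% |
| 20% | 90.4% | 11.9% |

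Repeat simulations gave 7.7% at 10% loss and 11.9% to 12.6% at 20%; one at 5% loss gave 6.2%.

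A closed form explains this. With a fraction f filled in, the within-group variance shrinks by a factor of about (1 − f), but the test still divides by 180. The true standard error exceeds the reported one by r = √(1 + (π/2 − 1)f²) / (1 − f).

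- At f = 0.10, r = 1.114. The nominal 1.960 acts as 1.960 / 1.114 = 1.759, so type I error is 7.9%.
- At f = 0.20, r = 1.264. The effective cut-off is 1.550, so type I error is 12.1%.

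The apparent 90% is therefore not power at the 5% level that the sample size calculation specifies.

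**The case against.** The strongest reply is that nothing in the protocol predicts loss. The loss-to-follow-up rule is conditional, and several provisions limit attrition. Children who stop the supplement stay in follow-up, those known to be moving are excluded where possible, and those who change school are pursued. Reading is tested in school by research staff after 16 weeks, so it does not depend on posted parent forms. Low loss is plausible. This stands: the protocol provides for losses, but a reader who infers that it expects them at some rate goes beyond the text.

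Second, with effect size, SD and sidedness unstated, 180 might already be rounded up or padded. That cannot be excluded. But the text presents 180 as what the calculation requires and mentions no margin, so the natural reading is that it is the bare number.

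Third, the shortfall is modest, and the protocol says that other outcomes needed smaller samples. This also stands. A reader might infer that the trial fails to deliver its power; the documents show only that the claim carries an unstated condition.

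Fourth, one might infer that a null result would come from an underpowered trial. The planned analysis does not fit that account: with median filling, the chance of rejection stays near 90% and the damage appears as false positives. This removes the null-result argument, but it does not rescue the power figure.

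**Conclusion.** The point holds in a limited form. The protocol equates the number required with the number randomised, states no allowance for loss, and has rules for missing outcomes. Its 90% is therefore a complete-follow-up figure presented without that condition.

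On the illustrative assumptions above, the shortfall is 1.5 points at 5% loss, about 3 at 10% and about 7 at 20%. The loss rates are assumed and the 0.34 SD is back-solved, so these figures show scale and do not estimate the trial's actual power. The type I error figures further assume normal data and losses completely at random. This is a power statement to correct, not a miscalculated total or a failed design.

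**What to change.** Keep 360 and rewrite the statement in the Sample Size section. It should:

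- say that 180 per group gives 90% power with complete follow-up only;
- give the sponsor's own effect size, SD and sidedness behind 180;
- give the expected loss and the power at the expected number of children with an observed reading outcome;
- not count children with imputed outcomes as information.

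A form of words, with the sponsor's figures in the brackets: *Randomising 360 children gives 90% power at the [one/two]-sided 5% level to detect a difference of [x] in standardised reading change (SD [y]) if every child supplies an outcome; with an expected loss of [z]%, power is [w]%.* The back-solved 0.34 SD should not be inserted as if it were the design value.

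The statement should not claim that baseline adjustment makes up the loss. The Analysis Plan specifies change scores, and the protocol gives no baseline correlation from which to work out a gain.

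The cost is one or two sentences and a slightly less favourable power figure. No extra children are needed. If the sponsor prefers to hold 90% at its expected loss, the total becomes 360 / (1 − loss), for example 400 at 10% or 450 at 20%.

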## Analysis Plan

The study will be analysed and reported following the ‘CONSORT’ guidelines (Consolidated Standard of Reporting Trials) (Moher, 2001).

On completion of the study post-intervention change score data from all children participating in Stage Two will be analysed on an intention to treat basis. Since the original protocol required that children be below the 20th centile on a standardized word reading test, ITT analysis of post-intervention change score data on these children will also be carried out. To further assess the importance of severity of reading impairment at baseline, similar analyses will be performed on children whose reading was assessed ≤ 10% level.

Missing data will be handled by imputing median values for missing data by treatment group.

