### British Ability Scale (BAS II) Word reading

This is an age standardized single word reading test from the British Ability Scales, normed on UK children It is administered to each child individually, taking only a few minutes to complete.

This kind of reading test was used successfully in the Oxford-Durham trial and was sensitive enough to show significant change over three months.

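### Change scores are fixed as the analysed quantity with no adjustment named for baseline, school or sex: unbiased, but less precise than an ANCOVA the protocol's own data would support

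*Protocol*

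**What the plan says.** The protocol's Analysis Plan states that "post-intervention change score data from all children participating in Stage Two will be analysed on an intention to treat basis". It repeats change scores for children below the 20th centile for word reading, and plans similar analyses for those at or below the 10% level. It names no test, model or covariate.

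Elsewhere the protocol has what an adjusted analysis needs:

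- Enrolment/Baseline Assessments and Baseline list word reading, digit recall and the Conners ratings before treatment. The same measures return post-intervention.
- Method of Randomisation describes a "minimisation algorithm to ensure balanced allocation of participants across the treatment groups for school", with a second factor, "sex of the child (an important prognostic factor").
- The end of Study Populations says only that possible sex differences will be explored.

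Sample Size is tied to reading change: "groups of 180 (i.e. a total n of 360) would be required, based on our standardized reading change".

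**The concern.** A change score fixes the slope on baseline at 1. When the true slope is below 1, this over-corrects any chance baseline difference between the arms and carries avoidable baseline noise into the comparison. ANCOVA estimates the slope instead.

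The design also balances the arms within schools as far as minimisation allows. If schools differ in 16-week change, that balance makes the treatment difference less variable. An analysis that omits school still counts the between-school variance in its standard error.

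At stake are some precision, protection from chance imbalance (most of all in the smaller reading subgroups) and a test that may be slightly conservative.

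**Working it through.** **1. The plan's own figure.** Sample Size gives 180 per group at 5% significance and 90% power, with the effect taken from an earlier trial ("Following the only previous randomized controlled study to assess reading ability, power calculations were performed to estimate likely group sizes"). No difference or SD is stated, so 180 cannot be reproduced. It can only be solved backwards (two-sided test assumed):

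d = (1.960 + 1.282) × √(2/180) = 0.342 SD of change.

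**2. Baseline adjustment, outcome not selected on.** With SD s at both times and baseline-to-follow-up correlation r:

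- change score: 2s²(1 − r)
- ANCOVA: s²(1 − r²)
- ratio: (1 + r)/2

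The protocol gives no r, so a range is assumed:

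| r | ANCOVA / change variance |
|---|---|
| 0.5 | 0.75 |
| 0.6 | 0.80 |
| 0.7 | 0.85 |
| 0.8 | 0.90 |
| 0.9 | 0.95 |

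At r = 0.6 the standard error falls by 1 − √0.80 = 11%.

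**3. Baseline adjustment, reading.** Stage Two children must lie in the lowest tertile for reading. Cutting a normal distribution at its lowest third leaves a variance of 0.28 of the original. Less baseline variance remains for the change score to mishandle, so the gain shrinks. With r the correlation before selection, the ratio is (1 − r²) / [(1 − r²) + 0.28(1 − r)²]. Power is Φ(0.342/√(2 × ratio/180) − 1.960).

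| r | ratio | power at 180 per group | total for the same precision (360 × ratio) |
|---|---|---|---|
| 0.70 | 0.953 | 91.3% | 343 |
| 0.80 | 0.970 | 90.8% | 349 |
| 0.85 | 0.978 | 90.6% | 352 |

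**4. Chance imbalance.** At 180 per group the SE of a baseline difference is √(2/180) = 0.105 baseline SD. A change score carries (r − 1) times the observed difference. For reading at r = 0.7:

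- a 2-SE imbalance is 2 × 0.105 × √0.28 = 0.112 in units of the unselected SD
- the estimate shifts by 0.3 × 0.112 = 0.033
- the SD of change is √(0.51 + 0.09 × 0.28) = 0.73, so the back-solved effect is 0.342 × 0.73 = 0.25
- the shift is about 13% of that effect

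ANCOVA removes it.

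**5. School.** The relevant ICC is that of the change score, because stable school differences cancel. If balance within schools were perfect, the variance would be overstated by 1/(1 − ICC): 11% at ICC 0.10 and 25% at 0.20, with test sizes of 3.9% and 2.8%. The design does not reach that limit, because the first 36 children are allocated without minimisation and the algorithm is not fully deterministic.

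The allocation was therefore simulated with 360 children, 50 schools, minimisation on school and sex after the first 36, and an assumed probability of 0.7 or 0.8 of following the algorithm. The variance that the unadjusted model reports was compared with the true variance of the difference:

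| ICC of change | variance overstated | size of a nominal 5% test |
|---|---|---|
| 0.10 | about 5–7% | about 4.2–4.4% |
| 0.20 | about 11–15% | about 3.5–3.9% |

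Whether schools enter one at a time or mixed moves the variance figures by less than two percentage points.

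**6. Cost of the school term.** In simulation with r = 0.7 and no school effect, adding 50 school dummies to ANCOVA with baseline and sex raised the mean SE from 0.0753 to 0.0771, about 2%. At r = 0.9 it rose from 0.0461 to 0.0472, which equals the change-score SE and so cancels the baseline gain. With a school ICC of 0.10 and r = 0.7, the dummies lowered the SE from 0.0750 to 0.0729. The sex term cost nothing measurable.

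**The case against.** **The text does not say unadjusted.** A reader might infer that the plan commits to a raw two-group comparison. It does not: it fixes the outcome scale and is silent on the model. A change score regressed on arm and baseline gives exactly the ANCOVA treatment effect, and covariates may stand in an analysis plan that is not shown. This stands, and silence alone is no error. What remains is that the protocol does fix a quantity, the change score, whose plain use is the less efficient choice.

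**There is no bias.** This also stands. Randomisation makes the change-score contrast unbiased, and on average its standard error already covers chance imbalance. The choice also matches the basis of the sample size. ANCOVA corrects the imbalance that actually occurs.

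**The gain is small where it counts.** It is tempting to take r = 0.6 and say that 90% power becomes 95%, or that 288 children would do the work of 360. The documents do not support this. The 90% and the 360 belong to reading, where selection limits the gain to about one point of power. For the other outcomes, Sample Size says smaller samples would have sufficed, so 90% is not their starting power.

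**The school effect is conditional.** This stands. It needs schools to differ in change, and the 11% and 25% figures need a perfect balance that this algorithm does not give.

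**Conclusion.** The point holds as a recommendation on efficiency and robustness. Baseline adjustment never loses precision asymptotically. It saves about 20% of variance at an assumed r of 0.6 for memory or behaviour, and about 2–5% for reading at r from 0.70 to 0.85. Ignoring school makes standard errors mildly too large, by about 5–15% of variance, if the ICC of 16-week change is 0.10–0.20.

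The protocol gives no correlation, SD, effect size, ICC or minimisation probability, so every size here rests on stated assumptions. The direction of the baseline gain does not depend on the value of r, given equal variances and r below 1. The documents do not support calling the planned analysis biased or invalid, or calling school adjustment free in every form.

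**What to change.** In the Analysis Plan, replace the reference to change-score data with a sentence to this effect: the 16-week score is compared between arms by ANCOVA, with the baseline value of the same measure and sex as covariates and school as a random effect, in the main analysis and both reading subgroups; change scores are shown descriptively.

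Use a random rather than a fixed school effect, because up to 50 fixed effects cost about 2% in standard error if schools do not differ. The cost is one sentence and a slightly more complex model, with no new data. It should be settled before unblinding.

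### The plan assesses the importance of baseline reading severity by repeating the treatment analysis in nested subsets, which cannot show whether the effect depends on severity

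*Protocol*

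**What the plan says.** The protocol's Analysis Plan sets three analyses in order.

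- **Full set.** "post-intervention change score data from all children participating in Stage Two will be analysed on an intention to treat basis".
- **Below the 20th centile.** The reason given is historical: "Since the original protocol required that children be below the 20th centile on a standardized word reading test". The same intention-to-treat change-score analysis is repeated in these children.
- **At or below the 10% level.** Here the reason is scientific: "To further assess the importance of severity of reading impairment at baseline, similar analyses will be performed on children whose reading was assessed" at or below that level.

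The word *further* ties the second set to the severity question as well. The section names no interaction term, no comparison of a subset with the remaining children, and no significance threshold for the subsets.

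The Sample Size section sizes only the full set: "with significance set at 5% and power at 90" per cent, "groups of 180 (i.e. a total n of 360) would be required", "based on our standardized reading change". It limits Stage Two to children "scoring within the lowest tertile on age-standardised measures of reading".

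**The concern.** The protocol fixes both a purpose (how much does baseline severity matter?) and a method (repeat the treatment comparison in ever more impaired subsets). The method does not serve the purpose. Whether the effect depends on severity is a question about a difference between treatment effects. Three separate effects in overlapping groups, each containing the next, do not estimate that difference.

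The subsets are also smaller than the full set, so their results will differ in precision and often in significance even when the effect is the same in every child. A reader who follows the plan as written has nothing else to go on. At stake is a conclusion about which children benefit, drawn from a pattern that sample size alone can produce.

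**Working it through.** **Inputs.** From the protocol: 180 per arm, 5% significance, 90% power, equal groups, reading in the lowest tertile at entry. Assumed: a two-sided test; the 10% level means the 10th centile; the shares f20 and f10 of the 360 in the two subsets. Children spread evenly over centiles 1 to 33 would give f20 = 20/33 = 0.61 and f10 = 10/33 = 0.30, about 218 and 109 children. Shares from 0.5/0.2 to 0.95/0.8 were tried.

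**1. The plan's own figure.** No effect size or SD is printed, so 180 per arm cannot be reproduced forwards. Solving n = 2(z₀.₉₇₅ + z₀.₉₀)²/d² backwards gives d = (1.960 + 1.282) × √(2/180) = 0.342 (0.308 if one-sided).

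**2. What the three analyses estimate.** Let θ₁ be the effect in children at or below the 10th centile and θᵣ the average effect in all others.

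- The 10% set estimates θ₁.
- The full set estimates f10·θ₁ + (1 − f10)·θᵣ.
- The gap between the two is (1 − f10)(θ₁ − θᵣ), with 1 − f10 = 0.70 under an even spread.

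No planned analysis estimates θ₁ − θᵣ. Comparing two of the planned results by eye shows a shrunken version of it, between overlapping samples, with no standard error.

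**3. A uniform effect, d = 0.342 in every child.** The expected z in a subset with share f is d√(90f).

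- Full set: 0.342 × √90 = 3.24; power Φ(3.24 − 1.96) = 90%.
- Below 20th, even spread: 3.24 × √0.606 = 2.52; power 71%.
- At or below 10th, even spread: 3.24 × √0.303 = 1.78; power 43%.

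The z-statistics of nested sets have correlation √(n_small/n_large): 0.778, 0.550 and 0.707 here. Simulation with these correlations (2 million draws) gives a significant full set with a non-significant 10% set in 48% of trials. The three results disagree on significance in 52%.

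**4. No effect in any child.** The same model gives, per outcome, the chance of any nominal two-sided p < 0.05 among the three, and the chance that a subset favours DHA while the full set does not.

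| Shares f20/f10 | Uniform effect: full set significant, 10% set not | No effect: any p < 0.05 | No effect: only a subset favours DHA |
|---|---|---|---|
| 0.5/0.2 | 60% | 11.7% | 3.3% |
| 0.61/0.30 | 48% | 11.0% | 3.0% |
| 0.8/0.5 | 28% | 9.7% | 2.3% |
| 0.95/0.8 | 9% | 7.7% | 1.3% |

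The third column includes the full-set test's own 5%.

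**5. What a direct test could detect.** For at or below the 10th centile against the rest, with an even spread, the standard error in SD units is √(2/54.5 + 2/125.5) = 0.229. Power is Φ(0.342/0.229 − 1.96) = 32% for an interaction as large as the whole planned effect, and about 85% for one twice that size. These figures are for a split at the 10th centile; a continuous baseline term was not evaluated.

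**The case against.** **The full set leads.** It comes first, it alone is sized, and the other analyses are introduced as additional. On that natural reading its type I error stays at 5%. This stands. A reader might infer that the plan roughly doubles the trial's false-positive chance. That needs all three results to count equally as evidence of benefit, which the protocol does not say. Nor does it give each subset its own 5% test; the only 5% belongs to the sample-size calculation. Order of testing and multiplicity rules may properly sit in an analysis plan that is not at hand.

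**The below-20th set has its own reason.** It is the population of the original eligibility criterion, and reporting it is transparent. This stands, and is a reason to keep the estimate.

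**The size is uncertain.** Children enter through a Key Stage 1 cut, teacher confirmation, names added by teachers and a baseline reading criterion, so the shares are unknown and the 48% should not be quoted without its range. Also, a significant full set with a non-significant 10% set would suggest that the most impaired benefit less. The opposite misreading, benefit only in the more impaired, arises in only about 2% of trials under a uniform effect with even spread. No rule in the protocol obliges anyone to read either pattern as a severity effect.

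**An interaction test is weak.** True, as step 5 shows. But a wide confidence interval displays that uncertainty, whereas separate subset results conceal it.

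None of this reaches the central point. The protocol states the question and the method, and an analysis plan that followed it faithfully would carry the mismatch forward.

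**Conclusion.** The point holds as one about method. Repeating the change-score analysis in nested subsets compares no level of severity with another, so it cannot show whether the effect depends on severity. This needs no numerical assumption.

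The size does. With a uniform effect at the 90%-power value and a two-sided 5% level, a significant full set and a non-significant 10% set would occur together in about 9% to 60% of trials over the shares tried, and in 48% with an even spread.

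The false-positive side is smaller and conditional. Only if all three results were taken as equal evidence of benefit would the chance of any nominal p < 0.05 under no effect be about 8% to 12% per outcome. If the full-set analysis leads, its error stays at 5%, and the chance that a subset alone falsely favours DHA is about 1% to 3% per outcome. The documents do not support the claim that the trial's overall error is inflated.

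**What to change.** In the Analysis Plan, replace the severity sentence with three statements.

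1. Severity is assessed by one treatment-by-baseline-reading interaction, using baseline BAS II word reading as a continuous variable, in a model of the outcome or change score that includes baseline reading as a covariate, reported with its confidence interval.
2. The below-20th estimate (the original-protocol population) and the at-or-below-10% estimate are kept, with confidence intervals, as supportive.
3. The efficacy conclusion rests on the full-set intention-to-treat analysis.

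No new data are needed, since word reading is already measured at baseline. The cost is a few sentences and a model with baseline reading and its interaction with treatment; the protocol now specifies only change scores, so that model must be written in. The downside is limited power: a null interaction is not evidence that severity is irrelevant, and the text should say so.
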